GM communicates straightforward with the enteric immune system, shaping immune tolerance and thus contributing to the modulation of immune reactions during inflammation (19). Conversely, upon pathogen invasion, dysbiosis or barrier break, the microbe-associated molecular patterns stimulate macrophages and dendritic cells to produce pro-inflammatory cytokines. In turn, the cytokine activate the adaptive immune cells, thus contributing to the breakdown of immune homeostasis (20), and typically, determines loss of the immune cells that keep the aggressiveness of the immune system in check, namely Tregs (12).

Several brain biological processes may be influenced by GM alterations. Germ free mice have been found to have an altered density, morphology and maturity of microglia, and treatment with a short chain fatty acids (SCFA) mixture restored the density and morphology of CNS immune cells, suggesting that GM can influence both the development and functions of microglia (12, 21).

In ALS, GM dysbiosis may facilitate the disease onset or drive its progression and related outcomes, in the presence of other risk factors. Alternately, the GM dysbiosis may be (further) altered by the disease presence and in some individuals contribute to disease progression, prognosis, also in terms of variable response to drug treatments (22).

An alteration in the intestinal bacterial flora as an external trigger could explain the rare cases of ALS in spouses or in some clusters (23).

Based on these premises, to treat GM dysbiosis through microbiota restoration would have the potential to interfere and slow ALS progression (24).

Our trial aims at evaluating the biological basis of a potential treatment for ALS (namely fecal microbiota transplantation, FMT) in order to plan a following efficacy study.

The primary objective is to evaluate if FMT augments Tregs' number in ALS patients, treated with FMT compared to the control arm and measured at baseline and at month 6.

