### Sample Size Estimation

Sample size was calculated considering as primary outcome measure the proportion of patients, in the transplantation group with respect to controls, displaying a “positive response” intended as an increase in the proportion of Treg by at least 20%. The null hypothesis states that FMT does not ameliorate significantly the proportion of positive responses in treated patients after the second FMT round, compared to their baseline and to control group. The alternative hypothesis is that FMT gives a proportion of positive responses in at least 50% of treated patients compared to a maximum 5% of positive responses in patients of the control group. The study was designed to refuse the null hypothesis with an alpha error of 0.05 and a power of 0.80 according to previously published statistical methods (26) and to known levels of Tregs in ALS patients, that typically display a slight reduction of Treg % (mean ± standard deviation: 2.1 ± 0.7) with respect to healthy controls with fast progressors patients having on average 31% fewer Treg (8, 27).

For this purpose, a population of 39 patients randomized in two treatment arms would suffice; taking into account an average drop out of 10%, a recruitment of 42 patients will be needed.

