### Outcome Measures

Primary outcome measure is the modification from baseline to month 6 in Treg number in transplanted ALS patients compared to the control arm (26).

Secondary outcome measures include the following:

✓ Biological outcome measures:–Change from baseline to month 3, 6, 9, 12 of the T cell distribution especially the ratio Treg/Th1 or Treg/Th17 comparing FMT arm and control arm (both blood—at each time point, and small intestine—only at 6 and 12).–Changes from baseline to month 3, 6, 9, 12 in inflammatory status (cytokine profile) comparing FMT and control arm (in blood and feces at each time point, and in CSF at month 6).–Changes from baseline to month 3, 6, 9, 12 between FMT arm and control arm in the following biomarkers: creatinine, albumin, CK, vitamin D, plasma/CSF neurofilament heavy/light chain protein.–Biological modifications from baseline to month 6 and 12 in the composition of saliva, gut and fecal microbiota (including SCFA) comparing FMT and control arm.✓ Safety: will be assessed in FMT and control arm considering the occurrence of AEs and modifications in physical examination, vital signs, body weight, and laboratory tests (biochemistry, hematology) during and following the treatment.✓ Clinical outcome measures:The following clinical variables will be compared between FMT and control arm:– Change from baseline to each time point (month 1, 3, 6, 9, 12) of ALSFRS-R.– Survival from onset and randomization to death or tracheotomy.– Change of Forced Vital Capacity (FVC) from baseline to each time point (month 1, 3, 6, 9, 12).– Frequency of procedures (PEG, NIV, IV) from baseline to month 3, 6, 9, 12.✓ Quality of life: will be assessed as the change in absolute and relative values of the Amyotrophic Lateral Sclerosis Specific Assessment Questionnaire (ALSAQ40) from baseline to month 6 and 12 in FMT and control arm.

The Table 3 shows the study flow chart.

**Table 3 T3:** Study flow chart.

	**Pre-treatment**		**Treatment**					**Follow up**			**Study end**
**Examinations**	**Screening**	**Baseline (W0)**	**FMT 1 (Rome)**	**M1**	**M3**	**M6**	**FMT 2 (Rome)**	**M7**	**M9**	**M12 (Rome)**	**M12**
**Time window**		** <3 weeks from screening**	** <4 weeks from screening**	**±3 days**	**±3 days**	**±3 days**	**±7 days**	**±7 days**	**±7 days**	**±7 days**	**≥7 days <4 weeks from M12**
Informed consent	x										
Medical history	x										
Inclusion exclusion criteria	x										

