As for clinical outcome measures, we will compare ALSFRS-R total score and subscores (bulbar, respiratory, gross, and fine motor) changes from baseline to each time point in treatment arm vs. control arm. Frequency of procedures (PEG, NIV, IV) will be compared from baseline to each time point in treatment vs. control arm. The comparison of clinical endpoint among arms will be carried out by using the logistic regression model. Results will be presented as odds ratios (OR) and 95%C.I. FMT will be considered effective in relation to controls whether the OR of positive results will provide a *p* < 0.05. Change in FVC during the study will be analyzed using a mixed model for repeated measures (MMRM). Difference between treatment groups and two-sided 95% CI will be estimated .Log-rank tests via Kaplan-Meier method will be employed to compare differences in tracheostomy-free survival between the two treatment arms (from onset and from randomization), while Cox's proportional hazard model will be used for adjusting for any possible unbalanced prognostic factors. Statistical significance will be set at 0.05 level for a two-tailed test. Last observation will be considered for patients with missing data.

Given the short duration of the study, an interim analysis of efficacy data is not scheduled. Nevertheless, to address safety concerns, a report including all relevant clinical data of patients will be sent by the Statistics Unit to an independent Data and Safety Monitoring Board for scheduled DSMB meetings (also through Skype) when 14 patients would have completed the second treatment and then every 6 months.

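### Data Analysis declares FMT effective on a logistic odds ratio for an undefined positive result, over some 37 secondary clinical comparisons, in a trial meant to prepare an efficacy study

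*Protocol article*

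**What the plan says.** The paragraph on clinical outcome measures in Data Analysis (protocol article) begins with "ALSFRS-R total score and subscores (bulbar, respiratory, gross, and fine motor) changes from baseline to each time point", compared between arms, and adds the frequency of procedures. It continues: "The comparison of clinical endpoint among arms will be carried out by using the logistic regression model", with results as odds ratios and 95% CIs. The decision rule follows: "FMT will be considered effective in relation to controls whether the OR of positive results will provide a" *p* < 0.05. Later in the paragraph, significance is set at 0.05, two-tailed.

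The outcomes and times come from Outcome Measures, where both are secondary: "Change from baseline to each time point (month 1, 3, 6, 9, 12) of ALSFRS-R" and "Frequency of procedures (PEG, NIV, IV) from baseline to month 3, 6, 9, 12".

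Three other analyses stand outside the logistic rule:

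- FVC: "Change in FVC during the study will be analyzed using a mixed model for repeated measures (MMRM"), with the between-arm difference and its 95% CI.
- Survival: log-rank and Cox.
- Treg response: a comparison between arms of the proportion with at least a 20% increase at month 6. No test is named.

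On purpose, the Introduction says that the biological basis of FMT is being evaluated "in order to plan a following efficacy study", and Anticipated Results repeats this.

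**The concern.** This is the only sentence in the document that says when FMT counts as effective, and it has three faults.

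1. **Model and outcome do not match.** A change in a score has no odds ratio until someone chooses a cut. The document gives a responder cut for Treg only. A cut for ALSFRS-R would have to be chosen later, and dichotomising discards information in a trial of 42 patients.
2. **The rule has no target.** No endpoint, visit or subscore is singled out, so any one significant result satisfies the sentence as written.
3. **The rule is detached from the design.** The trial was sized on Treg response and is presented as preparation for an efficacy study. The sentence nevertheless lets secondary clinical outcomes carry a declaration of effectiveness.

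At stake is a claim that FMT works in ALS resting on one of many unplanned-for comparisons, with the Treg result playing no part in it.

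**Working it through.** The plan gives no figure of its own for the clinical comparisons: no power, no event rate, no error rate. Its only sizing is for Treg response, and that holds up. At 50% versus 5% with 39 evaluable patients (26 vs 13 at 2:1), two-sided Fisher's exact test has 86.7% power, above the planned 80%.

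**Number of comparisons under the rule**

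- ALSFRS-R: total plus four subscores = 5 variables (Data Analysis); months 1, 3, 6, 9, 12 = 5 times (Outcome Measures). 5 × 5 = 25.
- Procedures: PEG, NIV, IV = 3; months 3, 6, 9, 12 = 4 times (Outcome Measures). 3 × 4 = 12.
- Total: 25 + 12 = 37.

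**Chance of at least one *p* < 0.05 with no effect**, taking independent tests each at its nominal level, 1 − 0.95^k:

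| k | Calculation | Result |
|---|---|---|
| 12 | 1 − 0.95^12 | 46% |
| 25 | 1 − 0.95^25 | 72% |
| 37 | 1 − 0.95^37 | 85% |

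The tests are positively correlated (a total with its own subscores, successive visits in the same patients), so these are upper guides. At the other extreme, perfectly correlated tests would give 5%. If only results favouring FMT count, each two-tailed test contributes 0.025: 1 − 0.975^25 = 47% and 1 − 0.975^37 = 61%, again for independent tests.

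**ALSFRS-R beside FVC.** Outcome Measures lists both as change from baseline at months 1, 3, 6, 9 and 12. Data Analysis gives FVC a repeated-measures model with a difference and 95% CI. For ALSFRS-R it names only logistic regression with odds ratios. Nothing in the document explains the different treatment.

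**Sparse procedure counts.** A zero cell makes the maximum-likelihood odds ratio zero or infinite, and its usual CI unusable. The document gives no PEG, NIV or IV rate, so a rate *p*, equal in both arms, has to be assumed. With 28 vs 14 patients,

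P(at least one arm has no events) = (1−p)^14 + (1−p)^28 − (1−p)^42.

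| Assumed p | Calculation | Result |
|---|---|---|
| 2% | 0.754 + 0.568 − 0.428 | 89% |
| 5% | 0.488 + 0.238 − 0.116 | 61% |
| 10% | 0.229 + 0.052 − 0.012 | 27% |

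At higher rates the problem fades: at 20% the chance of no event among 14 controls is 0.8^14 = 4%, and at 30% it is 1%. Table 1 excludes patients with previous ventilation, tracheotomy or gastrostomy and requires FVC of at least 70% predicted. Few events at the early visits are therefore plausible, but the document does not quantify this.

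**The case against.** **These are secondary outcomes, and their error control may sit in an analysis plan not shown.** That is fair, and missing multiplicity adjustment is not the point made here. The fault is in a sentence that is present: it attaches a declaration of effectiveness to those outcomes without saying which.

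**The 72% and 85% exaggerate.** They do if read as estimates. They assume independence and count significance in either direction; the one-directional figures are 47% and 61%, and correlation lowers all four. The word effective does imply an odds ratio in FMT's favour, so the missing direction is a matter of wording only.

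**The clash with the aim is loose language.** In part: Anticipated Results promises only preliminary clinical data. That supports removing the sentence, since the authors do not appear to want the claim that it licenses.

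**A stronger reading is tempting.** A reader might infer that the logistic analysis breaks down at the planned "a maximum 5% of positive responses in patients of the control group", because no control responder at all has probability 0.95^14 = 49% (51% with 13 controls), and so that the trial could miss the effect it was sized for. The documents do not support this. The 5% is the Treg responder rate, and Data Analysis compares those proportions without naming logistic regression. The phrase about positive results resembles the Treg wording, but it stands in the clinical paragraph. Even if logistic regression were applied to Treg response, the low power of 32% (26 vs 13) to 38% (28 vs 14) arises only with a Wald test that counts zero-cell tables as non-significant, and no section specifies a Wald test. A likelihood-ratio test from the same model has 92% to 93% power, and Fisher's exact test 87% to 91%.

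**Conclusion.** The point holds in this form: the effectiveness rule is wrong as written. It needs an odds ratio for a score with no stated cut, covers 37 comparisons by the document's own lists without choosing one, and is not tied to the primary Treg outcome of a study meant to prepare an efficacy trial. The false-positive chance is at most about 72% (ALSFRS-R alone) to 85% (with procedures) under independence in either direction, and lower by an unknown amount given the correlation. The zero-cell problem affects estimation of procedure odds ratios and depends on event rates that the document does not give. Nothing here shows that the primary Treg comparison is underpowered or mis-analysed. The matter should be corrected before analysis; it does not call the design into question.

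**What to change.** 1. **ALSFRS-R:** analyse change in the total and subscores by MMRM as for FVC, reporting the between-arm difference with its 95% CI. If a responder analysis is wanted as well, state the cut and the month in advance.
2. **PEG, NIV, IV:** compare proportions by an exact method or, if an odds ratio is wanted, use exact or Firth-penalised logistic regression with the matching CI.
3. **Effectiveness sentence:** replace it with wording such as: *The only confirmatory test is the primary comparison of Treg response between arms at month 6. Clinical outcomes are reported as estimates with 95% confidence intervals and support no claim of efficacy.*

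This changes text only, with no added patients, visits or measurements. The sponsor gives up an efficacy claim on secondary outcomes.

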## Abstract

**Background and Rationale:** Among the key players in the pathogenesis of Amyotrophic Lateral Sclerosis (ALS), microglia and T regulatory lymphocytes (Treg) are candidate cells for modifying the course of the disease. The gut microbiota (GM) acts by shaping immune tolerance and regulating the Treg number and suppressive function, besides circulating neuropeptides, and other immune cells that play in concert through the gut-brain axis. Previous mouse models have shown an altered enteric flora in early stage ALS, pointing to a possible GM role in ALS pathogenesis. Fecal Microbial Transplantation (FMT) is a well-known therapeutic intervention used to re-establish the proper microenvironment and to modulate enteric and systemic immunity.

**Methods:** We are going to perform a multicenter randomized double-blind clinical trial employing FMT as a therapeutic intervention for ALS patients (NCT0376632). Forty-two ALS patients, at an early stage, will be enrolled with a 2:1 allocation ratio (28 FMT-treated patients vs. 14 controls). Study duration will be 12 months per patient. Three endoscopic procedures for intestinal biopsies in FMT and control groups are predicted at baseline, month 6 and month 12; at baseline and at month 6 fresh feces from healthy donors will be infused at patients in the intervention arm. The primary outcome is a significant change in Treg number between FMT-treated patients and control arm from baseline to month 6. Secondary outcomes include specific biological aims, involving in-depth analysis of immune cells and inflammatory status changes, central and peripheral biomarkers of ALS, besides comprehensive analysis of the gut, saliva and fecal microbiota. Other secondary aims include validated clinical outcomes of ALS (survival, forced vital capacity, and modifications in ALSFRS-R), besides safety and quality of life.

**Expected Results:** We await FMT to increase Treg number and suppressive functionality, switching the immune system surrounding motorneurons to an anti-inflammatory, neuroprotective status. Extensive analysis on immune cell populations, cytokines levels, and microbiota (gut, fecal and saliva) will shed light on early processes possibly leading the degenerative ALS course.

**Conclusions:** This is the first trial with FMT as a potential intervention to modify immunological response to ALS and disease progression at an early stage.

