**Figure 1 F1:**
[figure not shown]
Picture of the study design.

The study will include 42 ALS patients with 2:1 allocation in 2 groups of subjects (28 FMT vs. 14 controls). Patients will be screened in the 15 days before baseline; then they will be randomly allocated to either FMT or control group. Randomization will be 2:1 (FMT: controls) and will be performed on line (using a computer-generated list of random number that will be centrally generated in the Statistical Unit). Given the heterogeneous ALS progression, patients will be stratified by ΔFS (progression rate), calculated at randomization according to Kimura et al. (25). Riluzole will be maintained during the entire study duration unless adverse events or patients' decision to withdraw. Endoscopic treatment will be performed within 21 days from randomization. Randomization number will not be re-used in any case. Estimated enrolment time is 18 months.

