### Study Population

The study will include probable laboratory-supported, clinically probable, or definite ALS according to revised El Escorial criteria (sporadic and familiar). Inclusion and exclusion criteria for the enrolment of the patients are presented in the Table 1.

**Table 1 T1:** Inclusion and exclusion criteria for patients.

**Inclusion criteria**	**Exclusion criteria**
– Patients diagnosed with a laboratory supported, clinically “probable” or “definite” amyotrophic lateral sclerosis according to the Revised El Escorial criteria – Sporadic or familial ALS – Female or male patients aged between 18 and 70 years old – Disease duration from symptoms onset no longer than 18 months at the screening visit – Patients treated with a stable dose of Riluzole (100 mg/days) for at least 30 days prior to screening – Patients with a weight >50 kg and a BMI ≥18 – Patients with a FVC equal or more than 70% predicted normal value for gender, height, and age at the screening visit – Patients able and willing to comply with study procedures as per protocol – Patients able to understand, and capable of providing informed consent at screening visit prior to any protocol-specific procedures – Use of effective contraception both for males and females	– Known organic gastrointestinal disease – History of gastrointestinal malignancy; ongoing malignancies – Use of immunosuppressive or chemotherapy within the past 2 years – Celiac disease and/or food (e.g., lactose) intolerance – Previous gastrointestinal surgery – Any condition that would make endoscopic procedures contraindicated – Acute infections requiring antibiotics – Antimicrobial treatment or probiotics 4 weeks prior to screening – Severe comorbidities (heart, renal, liver failure); severe renal (eGFR < 30 ml/min/1.73 m^2^), or liver failure or liver aminotransferase (ALT/AST > 2x Upper limit of normal), – Autoimmune diseases, inflammatory disorders (SLE, Rheumatoid arthritis, connective tissue disorder) or chronic infections (HIV, hepatitis B, or C infection, Tuberculosis) – Abuse of alcohol or drugs – Participation in clinical trials <30 days before screening – Existing blood dyscrasia (e.g., myelodysplasia) – White blood cells <4,000/mm3, platelets count <100,000/mm3, hematocrit <30% – Patients who underwent non-invasive ventilation, tracheotomy and /or gastrostomy – Women who are pregnant or breastfeeding

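### With few deaths or tracheotomies likely in 28 vs 14 patients, a Cox model adjusted for whatever proves unbalanced may give no finite hazard ratio, and the log-rank p-value is unreliable at two events

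*Protocol article*

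**What the plan says.** Under Outcome Measures, one of the secondary clinical outcomes is "Survival from onset and randomization to death or tracheotomy". The Data Analysis section fixes the test: "Log-rank tests via Kaplan-Meier method will be employed to compare differences in tracheostomy-free survival between the two treatment arms", on both time scales. It then says that "Cox's proportional hazard model will be used for adjusting for any possible unbalanced prognostic factors", and that "Statistical significance will be set at 0.05 level for a two-tailed test".

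The size of the comparison is set in the Study Design text: "The study will include 42 ALS patients with 2:1 allocation in 2 groups of subjects (28 FMT vs. 14 controls". The Abstract sets follow-up: "Study duration will be 12 months per patient". Table 1 restricts entry to early disease: "Patients with a FVC equal or more than 70% predicted normal value" and "Disease duration from symptoms onset no longer than 18 months at the screening visit".

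The article gives no expected number of deaths or tracheotomies. It does not say whether the log-rank p-value is asymptotic or exact, and it does not say what happens to the hazard ratio if one arm has no event.

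**The concern.** Early-stage patients followed for one year may produce only a handful of events among 42 people. A Cox model fitted by ordinary partial likelihood has no finite treatment estimate when every event is in the same arm: the hazard ratio runs to zero or infinity and the Wald interval means nothing. Adding covariates makes this worse. Here they are also picked because they look unbalanced in the data at hand, so the adjusted model is not fixed in advance.

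The log-rank test has a narrower weakness. With 2:1 allocation and two or three events, its normal approximation is coarse and asymmetric.

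What is at stake is the reading of the hardest clinical outcome in a trial meant to prepare an efficacy study. A hazard ratio that does not exist, or a nominally significant survival difference resting on two events, would be poor material for that step.

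**Working it through.** **Inputs.** 28 FMT and 14 control patients (Study Design); 12 months per patient (Abstract); log-rank and adjusted Cox, two-tailed 0.05 (Data Analysis). The 12-month risk r is not in the document. I assume 5% to 20%, equal in both arms (no treatment effect), with no dropout. Expected events are 42r, about 2 to 8.

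**Plan's own figure.** There is none to reproduce. The stated 39 patients, raised to 42, were sized for the Treg responder outcome. No event count, hazard ratio or power is given for survival.

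**1. Chance that all events fall in one arm.** Among trials with at least one event:

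[(1−r)^14 + (1−r)^28 − 2(1−r)^42] / [1 − (1−r)^42]

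At r = 0.05: (0.4877 + 0.2378 − 2 × 0.1160) / (1 − 0.1160) = 0.4935 / 0.8840 = 0.558.

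| Risk r | Expected events | All in one arm, given any event | Control arm only (HR 0), all trials | FMT arm only (HR infinite), all trials |
|---|---|---|---|---|
| 5% | 2.1 | 56% | 12% | 37% |
| 10% | 4.2 | 26% | 4% | 22% |
| 15% | 6.3 | 11% | 1% | 10% |
| 20% | 8.4 | 5% | 0.2% | 4% |

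Given the number of events, the chance is 54% at two, 19% at four and 7% at six. At two events: (14/42)(13/41) + (28/42)(27/41) = 0.106 + 0.439 = 0.545.

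**2. Log-rank at two control events, none on FMT** (full risk sets from randomization).
- Expected control events: 14/42 + 13/41 = 0.650, so O − E = 1.350.
- Variance: (14/42)(28/42) + (13/41)(28/41) = 0.2222 + 0.2165 = 0.439.
- z = 1.350/0.662 = 2.04, two-sided p = 0.042.
- Null probability of this split given two events, which is also the exact p: (14/42)(13/41) = 91/861 = 0.106.

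Three control events against none stay significant either way: ordinary p = 0.011, exact p = (14 × 13 × 12)/(42 × 41 × 40) = 0.032.

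**3. The direction of harm.** Six FMT events against none give ordinary p = 0.069; seven give 0.047. The exact p for seven is 0.0439 + 0.0313 = 0.075, because equally extreme outcomes on the benefit side are counted; eight give about 0.037. The ordinary test therefore needs seven FMT events against none, and the exact test eight.

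**4. Overall error of the ordinary log-rank,** enumerating all event orders and averaging over the binomial number of events:

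| Risk r | Two-sided size | Towards FMT benefit | Towards harm |
|---|---|---|---|
| 5% | 3.8% | 3.8% | 0.0% |
| 10% | 3.8% | 3.4% | 0.4% |
| 15% | 4.3% | 3.0% | 1.2% |
| 20% | 4.8% | 3.1% | 1.7% |

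**5. How often the two-against-none result arises.** Under no effect its unconditional chance is 91r²(1−r)^40: 2.9% at 5% risk, 1.3% at 10%, 0.3% at 15%.

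**6. What an exact log-rank changes** (unstratified). At 10% risk, false benefit is 2.7-2.8% and false harm 0.1%. At 15-20% risk, false benefit stays about 3.2% while false harm falls to 0.6-1.2%.

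**The case against.** The strongest reply is that log-rank plus Cox is the conventional choice, and that exact p-values, penalisation and interval type are commonly left to an analysis plan, which is not shown. For the log-rank this largely stands: the article does not call the test asymptotic, so the p-value point is a caution about how the test is usually run. It stands less well for the Cox model, because the article itself fixes adjustment by observed imbalance.

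A reader might infer that the plan inflates the false-positive rate. It does not: the two-sided size stays below 5% at every risk examined. The 10.6% applies only given exactly two events, and the one-sided excess towards benefit is 3.0-3.8% against 2.5%. Nor is the lean uniform: at seven events, false harm (4.4%) exceeds false benefit (3.1%).

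A reader might also infer that a degenerate hazard ratio favours FMT. Usually it does not: with twice as many FMT patients, the arm holding all the events is more often FMT.

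The event rate is assumed. Early-stage entry makes few events plausible but does not quantify them, and the article itself describes ALS as progressing fast. At 15-20% risk the Cox problem becomes uncommon.

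The value 0.042 is also fragile. If two FMT patients leave before the first event (14 vs 26) it becomes 0.0496; if three leave, 0.054. It applies from randomization only; from onset the risk sets differ.

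Finally, an exact test does not cure the asymmetry and makes harm slightly harder to declare.

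**Conclusion.** The concern holds in a limited form. The better-supported part is the Cox model. If the 12-month risk is about 5-10%, which is an assumption, roughly one trial in four to one in two with any event would give a zero or infinite hazard ratio. With two to four events, no set of covariates selected for imbalance can be supported. At 15% and 20% risk the degenerate case falls to 11% and 5%.

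The log-rank part is narrower: the ordinary p-value should not be trusted at exactly two events (0.042 against 0.106). This is not a general loss of error control, and the documents do not support calling it one.

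Survival is one of many secondary outcomes, the primary conclusion on Treg is untouched, and the article promises only preliminary clinical data. Priority is optional to moderate.

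**What to change.** In the Data Analysis section:
- Replace the imbalance-driven Cox model with a Firth-penalised Cox model containing treatment and the stratification factor ΔFS only, with a profile-likelihood 95% interval.
- Report the number of deaths and tracheotomies per arm beside it.
- When events are very few, show an exact (permutation) log-rank p-value next to the ordinary one, and claim no survival benefit on the asymptotic value alone. If the permutation is done within ΔFS strata, its value at two against none need not be 0.106, which is the unstratified figure; the article gives no stratum sizes.

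The cost is a change of wording and standard software, with no new data. The downsides should be stated. The penalised estimate will have a wide interval at these event counts. The exact test is more conservative overall (at 10% risk, about 2.9% two-sided against 3.8%) and leaves the 2:1 asymmetry in place, needing eight rather than seven FMT events against none to show harm. Safety should therefore be judged on the event counts and not on that p-value.
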